### Analysis

2.7

The primary objective of this trial is to investigate the non-inferiority of the intervention group compared to the control group in terms of changes in speech intelligibility from baseline to post-treatment. The hypothesis is as follows:

$$H_{0}:\mu_{t}-\mu_{c}<\delta \;vs\;H_{1}:\mu_{t}-\mu_{c}\geq \delta$$

Where *μt* is the mean change in speech intelligibility score in the intervention group using the digital speech therapy application, and *μc* is the mean change in the control group receiving conventional speech therapy. It is assumed that there is no difference between the two groups, and this study seeks to establish the non-inferiority of the groups. The non-inferiority margin *δ* is set at 19 points, based on the assumption that a difference of 1 to 19 points on the speech intelligibility scale is clinically non-inferior (45).

The sample size required for the non-inferiority trial was determined using a statistical formula (46). This involved setting the significance level (alpha) to 0.025 for a one-sided test and targeting a power of 80% (*β* = 0.2) (47) with a standard deviation of 24.9 (48). This calculation revealed that 28 participants are required for each group. A total of 56 participants are required for the trial. To account for a possible dropout rate of 30%, we aim to recruit a total of 76 participants, with 38 participants in each group.

$$n=\frac{2{\left(z_{\alpha }+z_{\beta }\right)}^{2}\sigma^{2}}{{\left(\mu_{t}-\mu_{c}-\delta \right)}^{2}}\approx 28$$

Analyses will be performed using SPSS software (version 27; IBM Corp., Armonk, New York). Descriptive statistics will summarize the demographic data and outcome measures. For interval estimates, 95% confidence intervals will be provided. An intention-to-treat (ITT) analysis will include all randomized participants. Additionally, we will conduct a per-protocol (PP) analysis which includes only participants who fully adhered to the intended protocol.

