First, the Shapiro–Wilk test will assess of the normality of the distributions. Based on these results, the appropriate parametric (independent two-sample t-test) or non-parametric test (Mann–Whitney U test) will be chosen for between-group comparisons. Then, mixed repeated-measures analysis of variance (ANOVA) will evaluate the changes over time within subjects and between groups, with fixed effects for time, group, and their interactions. Mauchly’s test will check sphericity by applying the Greenhouse–Geisser, if necessary. For significant findings, Tukey’s HSD tests will conduct post-hoc analyses with Bonferroni correction to control for the overall type I error rate at 0.05. The benchmark for statistical significance is set at *p* < 0.05.

We will address missing data using multiple imputation techniques and the Last Observation Carried Forward (LOCF) method. This approach aims to minimize bias and ensure the robustness of efficacy outcomes (49). Subgroup and sensitivity analyses will be conducted to explore the effects of participant characteristics and institutional factors on the primary efficacy results. In addition to the primary analysis, we will conduct subgroup analyses to examine the efficacy of our digital speech therapy application in various settings. Subgroup analyses include comparing its use during hospitalization with post-discharge home use. These analyses aim to provide a deeper understanding of how the setting influences the effectiveness of the therapy.

Furthermore, additional subgroup analyses will focus on the effects of the interventions across different stroke phases. Since participants are stratified based on the onset period of their stroke into acute to subacute, and chronic phases, these subgroup analyses will explore how the efficacy of the intervention varies between these two distinct stroke phases. We will perform regression analyses within each group stratified by the stroke onset period. If the statistical analysis reveals significant mean differences between various groups, post-hoc tests will be conducted to identify the specific groups among which these differences exist. This approach will provide valuable insights into whether the timing of a post-stroke intervention influences the efficacy of digital speech therapy. No interim analyses are planned to maintain the integrity of the non-inferiority margin or control for type I error rate.

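### The primary ITT analysis is not fixed in advance: a normality pre-test picks the test, and its rank branch gives no mean difference to pool across imputations or compare with the 19-point margin

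*Protocol article*

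**What the plan says.** All of this is in section 2.7 (Analysis) of the protocol article unless another place is given.

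- **Hypothesis.** Non-inferiority is stated for the between-arm difference in mean change in speech intelligibility, with a margin of 19 points. 95% confidence intervals are promised for interval estimates.
- **Analysis set.** "An intention-to-treat (ITT) analysis will include all randomized participants". A per-protocol analysis is added.
- **Choice of test.** "First, the Shapiro–Wilk test will assess of the normality of the distributions". Then: "Based on these results, the appropriate parametric (independent two-sample t-test) or non-parametric test (Mann–Whitney U test) will be chosen for between-group comparisons". A mixed repeated-measures ANOVA follows.
- **Missing data.** "We will address missing data using multiple imputation techniques", and the same sentence goes on to name LOCF. The text does not say which of the two is primary.
- **Visits.** Table 2 (section 2.6) gives the primary outcome one post-baseline assessment, at 4 weeks.
- **Dropout.** The sample size is raised to 76 (38 per arm) for a possible 30% dropout.

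**The concern.** The plan commits the same primary outcome to two things that do not fit together. One is a test chosen from the data. The other is multiple imputation, which needs the same quantity, with its standard error, from each completed dataset. The t-test branch provides that and the Mann–Whitney branch does not. Because MI and LOCF are unranked as well, the text as written allows several ITT results: t-test or rank test, each under MI or LOCF.

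The trial has one confirmatory question, whether the mean change under the application falls short by less than 19 points. If the rank branch is selected, the planned output is a rank statistic and a p-value, and the analyst must improvise a route back to a mean difference after seeing the data. That is the freedom that prespecification is meant to remove.

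**Working it through.** **1. What the design is built on.** Inputs from section 2.7: one-sided alpha 0.025 and power 80%, SD 24.9, margin 19, true difference 0.

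n per arm = 2(z_α + z_β)²σ² / margin² = 2 × (1.960 + 0.842)² × 24.9² / 19² = 26.96, so 27.

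The article states 28, which agrees to within one patient per arm. The sample size is therefore that of a mean difference and its standard error.

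**2. How much rests on imputation.** At the planning allowance, 0.30 × 76 = 22.8, about 23 patients (11.4 per arm), would lack a week-4 value. With no intermediate visit, LOCF can only carry baseline forward, which sets their change to zero. MI draws values from a model. The two can give different answers.

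**3. What each branch supplies.** Rubin's rules take an estimate Q and a variance U from each of M completed datasets. They report the mean of Q with total variance T = Ū + (1 + 1/M)B, where B is the between-imputation variance of Q.

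| Planned step | Q and U for the mean difference? | Comparable with 19 points? |
|---|---|---|
| t-test on change | Yes | Yes, through its interval |
| Mixed ANOVA, two time points | Yes: the 1-df group-by-time F equals the squared t on change | Yes, through that contrast |
| Mann–Whitney U | No: rank statistic and p-value | No |

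The gap is in the third row, and it does not depend on where the normality check is run.

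**4. How often the gate matters.** The simulation used 38 per arm, SD 24.9 and 600 trials per scenario. The following are assumptions not given in the article: values missing completely at random; 20 imputations from a normal model with one auxiliary variable correlated about 0.5 with the outcome; Shapiro–Wilk at 0.05 in each arm; Mann–Whitney chosen if either arm rejects; four outcome shapes.

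*(a) Normality checked once, on observed data: share of trials sent to the rank branch.*

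| Outcome shape | 5% missing | 10% | 30% |
|---|---|---|---|
| Normal | 9% | 9% | 10% |
| Mild skew | 56% | 58% | 48% |
| Marked skew | 98% | 95% | 91% |
| Exponential | 100% | 100% | 100% |

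*(b) Normality checked in every imputed dataset: share of trials in which the 20 datasets do not all select the same test.*

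| Outcome shape | 5% missing | 10% | 30% |
|---|---|---|---|
| Normal | 17% | 30% | 54% |
| Mild skew | 36% | 57% | 80% |
| Marked skew | 10% | 23% | 70% |
| Exponential | 0% | 2% | 28% |

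Under (a) the datasets cannot disagree, but the rank branch is reached often once the outcome is skewed. Some skew is plausible, since section 2.6.1 defines the score as a percentage of words transcribed correctly.

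**The case against.** The strongest reply is that no sentence places Shapiro–Wilk inside each imputed dataset. Missing data come in a separate, later paragraph, and one check on observed data is at least as natural a reading. Under it the between-imputation conflict is zero by construction. **This stands**, and table (b) is therefore conditional.

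A reader might go further than the text allows in three ways:

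- *That the imputed datasets will select different tests.* The text does not require a check in each dataset. Even with one, conflict is a risk and not a certainty.
- *That the plan provides nothing to pool.* The t-test and the 1-df ANOVA contrast both do. Only the rank branch fails.
- *That ITT has no single result.* LOCF, which is also named, yields one completed dataset and one verdict. The accurate statement is that the result is not settled beforehand.

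It is also fair that table (b) counts a trial as split when a single imputation differs. In a rerun with normal data at 30% missing (assumed baseline correlation 0.2 to 0.8), splits occurred in 49% to 58% of trials. In 53% to 57% of those, only one or two of the 20 datasets were in the minority. Pooling the t-test throughout gave 94% to 95% interval coverage. So no inflation of the error rate has been shown. The coverage figure also supports pooling the mean difference without a gate.

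The last argument is that the imputation model, number of imputations and pooling rule belong in a statistical analysis plan, which is not shown. That is right, and their absence is not criticised here. The switch is different, because it is a rule the article states. An analysis plan would have to override it, since more detail would leave it in place. One could derive a shift estimate and interval from the rank test, but the article names none, and it equals the mean difference only under a pure location shift.

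**Conclusion.** The point holds in a limited form and should be corrected. The article lets a normality pre-test choose the primary comparison, and one of the two outcomes of that choice cannot deliver the pooled mean difference and interval that its own hypothesis needs. Two unranked missing-data methods widen the choice. The ITT result is therefore not fixed in advance and may not address the 19-point hypothesis.

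Size at 30% missing: with one check on observed data, the rank branch is reached in 10% of simulated trials with a normal outcome, and in 48% to 100% with the skewed shapes. With a check in each imputed dataset, which the text does not state, choices split in about 28% to 80%. At 5% missing the split range is 0% to 36%.

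These figures rest on assumed outcome shapes, an assumed imputation model and a dropout rate that is a planning allowance. That the rank branch supplies no mean difference rests on none of them. The stated sample size is unaffected.

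**What to change.** Drop the normality gate for the primary analysis. In each imputed dataset, fit one prespecified linear model of the outcome on arm, with any covariates named in advance. Pool the arm coefficient and its standard error by Rubin's rules, and compare the pooled 95% confidence interval with the margin. This makes MI the primary method, so say so and label LOCF a sensitivity analysis. Keep any rank test as a sensitivity analysis too, for example on complete cases.

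**Cost.** The change is to wording only, with none to sample size, visits or conduct. What is lost is the automatic switch to a rank test when the data look non-normal. With 28 to 38 patients per arm, a mean difference and its interval tolerate moderate non-normality, and the rank sensitivity analysis would show whether the conclusion depends on it.

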### Inclusion procedure

2.2

The principal investigator will screen and exclude participants with abnormalities in oral structures based on speech assessments. A comprehensive list of eligibility criteria is presented in Table 1. Stroke specialists will identify participants with dysarthria using the National Institute of Health Stroke Scale (NIHSS) criteria (23). The NIHSS is utilized for its ease of administration and standardized approach, which minimizes interpersonal variation in assessments. Also, the sub-section of “10. speech” is suitable for initially identifying dysarthria severity in stroke patients. We aim to recruit participants with both mild-to-moderate and severe dysarthria. Mild-to-moderate dysarthria is characterized by slurred speech that remains understandable, and severe dysarthria involves mostly unintelligible speech or the inability to speak without evidence of aphasia. The eligible participants will be referred to a research coordinator to verify their suitability for the trial. To educate the participants, the principal investigator will provide detailed information about the study, such as intervention options, associated risks, and expected benefits. All recruitment and screening processes will be thoroughly documented.

Participants will be clearly informed that they have the right to withdraw from the study at any point without any consequences to their future medical care. Withdrawal criteria will include voluntary withdrawal by the participant, a usage rate falling below 40%, a need for immediate medical care that precludes continued participation, and any adverse events that are directly related to the digital therapy application. Additionally, the research team reserves the right to withdraw participants if there is significant noncompliance with the study protocol or if their health status changes to the extent that continued use of the application is deemed unsuitable or unsafe.

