Subsequently, the participants will undergo a comprehensive assessment for post-stroke dysarthria. Psychological well-being questionnaires will also be administered to assess depression and quality of life. Participants will engage in the post-evaluation phase 4 weeks after the baseline assessment. We will repeat the speech assessments and psychological questionnaires from the baseline evaluations. Additional evaluations of usability and adherence rates will be conducted.

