Maintaining long-term commitment to post-stroke treatment can be challenging (58, 59). Patients may exercise less frequently than suggested (60), struggle to achieve daily treatment goals (61), or discontinue therapy entirely (59). Digital solutions offered for comfort in patients’ homes are expected to encourage more intensive speech treatment (6) and better adherence. Digital speech therapy applications enable easier access to speech therapy, increase engagement, and may reduce costs (62, 63). However, this study has several limitations. First, the limited sample size might limit the applicability of our results. Second, our digital speech therapy application is designed exclusively for Koreans and targeted at native Korean speakers. This language limitation could limit the generalizability to non-Korean populations. Third, the lack of direct supervision by clinicians or SLPs in digital speech therapy interventions could affect patient motivation and result in higher dropout rates (59, 64). Finally, a significant challenge arises from the high proportion of older participants, which is typical in stroke patient demographics (65). Despite considering the design of our application for the elderly population, these participants may experience lower usability and adherence to digital treatment because of their unfamiliarity with digital technology.

Despite these limitations, this study has several strengths. First, it aims to provide new evidence for the use of digital speech therapy in the treatment of post-stroke dysarthria. This could increase the adoption of digital treatment in the field. Second, the study is designed to investigate whether a digital speech therapy application is effective and feasible for stroke participants, regardless of their severity and recovery stage.

In conclusion, this trial explores the efficacy and feasibility of digital speech therapy applications in treating post-stroke dysarthria. Our study aims to provide significant insights that will aid future research by refining effect size estimates and enhancing power analysis. By addressing the complexities of post-stroke speech therapy through a digital application, we expect to enhance treatment strategies. Through our trial, we expect to be able to provide evidence of digital therapeutics for the treatment of post-stroke dysarthria.

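### Neither multiple imputation nor LOCF is a conservative check on non-inferiority with a single post-baseline visit, so the stated pair does not give the robustness the plan aims for

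*Protocol article*

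**What the plan says.** Section 2.7 (Analysis) of the protocol article states: "We will address missing data using multiple imputation techniques and the Last Observation Carried Forward (LOCF) method". It names no primary method of the two. The next sentence gives the purpose: "This approach aims to minimize bias and ensure the robustness of efficacy outcomes". The sensitivity analyses are then described: "Subgroup and sensitivity analyses will be conducted to explore the effects of participant characteristics and institutional factors on the primary efficacy results". The ITT set is all randomized participants. The per-protocol set keeps only full adherers, so it leaves drop-outs out as well.

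Section 2.6 (Outcome measurements) and Table 2 give one post-baseline speech assessment: "Participants will engage in the post-evaluation phase 4 weeks after the baseline assessment".

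Three other statements bear on who will be missing:
- Section 2.7, sample size: "To account for a possible dropout rate of 30" per cent, 38 are recruited per group.
- Section 2.2 (Inclusion procedure): "Withdrawal criteria will include voluntary withdrawal by the participant, a usage rate falling below 40" per cent. The article does not state whether week-4 scores are still collected after such a withdrawal.
- Section 3 (Discussion): lack of direct supervision in digital therapy "could affect patient motivation and result in higher dropout rates". The same section also says that digital solutions used at home "are expected to encourage more intensive speech treatment (6) and better adherence".

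**The concern.** Each of the two named methods makes a fixed assumption about the unseen week-4 score. With no interim score to learn from, standard MI gives a lost app user roughly the change of app completers who look alike on observed data. LOCF carries the baseline forward, so every drop-out in either arm has a change of exactly zero.

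If app users leave because they engage poorly and do worse than completers, MI puts the app mean too high. In a non-inferiority trial that lifts the lower confidence limit away from -19, towards the claim. LOCF does not correct this, because it also removes any gain from control drop-outs and so shrinks a true deficit of the app. Agreement between the two would then look like robustness without being evidence of it. The sensitivity analyses named vary participant characteristics and institution, and the per-protocol analysis drops the same people, so none of them tests the assumption.

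**Working it through.** **Inputs from section 2.7.** Margin 19 points (read as a lower limit of -19 for app minus control), SD 24.9, one-sided alpha 0.025, power 80%, 38 per group, dropout allowance 30%.

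**Assumed, because the article gives no figure.** The allowance is taken as the share of missing week-4 scores, equal in both arms. D is the net app penalty: how far app drop-outs fall below app completers, minus the same shortfall in the control arm. The true ITT difference is set at -19, where the false-claim rate should be 2.5%. The imputation model is taken to hold no strong auxiliary predictors, so MI is close to the completer contrast.

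**Plan's own figure.** n = 2 × (1.960 + 0.842)² × 24.9² / 19² = 26.96, so 27 per group against the stated 28. The inputs are the ones the plan used.

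**Bias and false-claim rate under MI.** Completers per arm: 38 × 0.70 = 26.6. SE = 24.9 × √(2/26.6) = 6.83. MI overstates the app-minus-control difference by 0.30 × D, so the false non-inferiority rate is Φ(0.30 × D / 6.83 − 1.96).

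| Net penalty D | Bias (points) | False non-inferiority |
|---|---|---|
| 0 | 0 | 2.5% |
| 5 | 1.5 | 4.1% |
| 10 | 3.0 | 6.4% |
| 15 | 4.5 | 9.7% |
| 19 | 5.7 | 13.0% |

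A simulation with random numbers of drop-outs and a pooled t interval agrees: 2.5%, 4.0%, 6.4% and 12.8% at D = 0, 5, 10 and 19.

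**Range over the missing share.**
- 15% missing in each arm: 4.3% at D = 10 and about 6.6% at D = 19.
- 26.3% missing (28 completers out of 38): 5.9% at D = 10.
- 40% missing in the app arm and 20% in control, with control drop-outs like control completers: 8.4% at D = 10.

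**How far the imputed app values must fall to reverse a claim.** With 26.6 completers per arm the 95% half-width is 13.7. The tipping shift is (19 − 13.7 + observed difference)/0.30, holding the half-width fixed:
- observed difference 0: 17.6 points;
- observed difference -3: 7.6 points.

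**LOCF.** With 30% set to zero change in each arm, a true difference of -19 and D = 0, the expected estimate shrinks to 0.70 × (−19) = −13.3. For control changes of 10 to 30 points, simulated false non-inferiority is 15% to 20% with the number of drop-outs fixed at 11 per arm, and 19% to 22% with it random. This arises before any drop-out penalty is assumed. Among the scenarios run, LOCF stayed at or below 2.5% only with 50% app and 10% control drop-out and a control change of 30 points (0.4% at D = 0, 1.8% at D = 10, but 5.1% at D = 20).

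**The case against.** **The protocol does not predict the pattern.** A reader might infer that it expects app users to drop out through lost motivation. It does not: section 3 says only that this could happen, and its one stated expectation is better adherence. The under-40% usage criterion in section 2.2 is firmer support, because it can tie missing scores to poor use, but only if outcomes are not collected after withdrawal.

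**The asymmetry is assumed.** The control is a self-administered workbook, and section 1 links monotonous traditional therapy to reduced adherence. Both arms receive close follow-up. If drop-outs are equally worse in both arms and missingness is equal, the MI contrast is unbiased and the rate stays at 2.5%. If app drop-outs are 10 points worse and control drop-outs 5, it is about 4.1%. This stands, and is why the rates are given by net penalty.

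**The imputation model could include app use.** Section 2.6.2 says use is tracked. A model with a good use measure would reduce the bias; the figures above assume no such help.

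**The scenario is extreme.** If completers do equally well in both arms, app drop-outs would have to be 63 points worse (19/0.30) before the true difference reached -19. That is correct, and it limits how often a wrong claim would arise. The conclusion, however, turns on the confidence limit, which crosses -19 at much smaller shifts.

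**This is detail for the SAP.** The absence of a tipping-point analysis from an article is no fault in itself, and a SAP not shown may contain one. A reader might also infer that a false claim would go unchallenged. The documents do not support that: MI and LOCF make different assumptions and can disagree. What remains is that the article ties robustness to this pair, and the pair does not provide it.

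**Conclusion.** The point holds in a limited form. The article states robustness as an aim, not as a demonstrated property, but the means it names do not serve that aim for non-inferiority with one post-baseline visit. MI leaves the key assumption untested, and LOCF usually errs towards the claim.

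The size depends on unstated quantities: from no inflation when drop-outs fall short equally in both arms to about 13% against 2.5% at a net app penalty of 19 points, with 30% missing per arm and a true difference at the margin. It is smaller with less missing data or an informative imputation model. The documents do not show that the bias will occur. They show that it could, and that no analysis named in the article would measure it. This should be changed before unblinding; it does not by itself invalidate the design.

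**What to change.** In section 2.7:
1. Name MI as the method for the ITT comparison, and do not rely on LOCF as the robustness check.
2. Replace the robustness sentence with a pre-specified delta-adjusted MI. Lower the imputed change of every app participant without a week-4 score by 0, 5, 10, 15 and 19 points, leaving control imputations unshifted.
3. Show a grid in which control imputations are shifted too, so that the one-sided assumption is visible.
4. Report the shift at which the lower 95% limit crosses -19. Describe non-inferiority as robust only if it survives a shift whose numerical value is written into the plan before unblinding.

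The cost is a few lines of text and slightly more analysis, with no new data or participants. The downside is that the claim may have to be reported as fragile. The one-arm shift alone is deliberately severe on the app, so it should be read with the grid.

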### Randomization

2.3

Participants will be randomly allocated in a 1:1 ratio to either the intervention group or control group. An independent third-party entity will oversee the randomization process to ensure impartiality.

Additionally, the trial will stratify participants based on the onset period of their stroke: acute to subacute phase (within 1 month of onset) and chronic phase (from 1 month to 6 months of onset) (24). After confirming participants’ eligibility, we will assign each participant a sequential number for group allocation. For each stratum, we will actively allocate participants in a 1:1 ratio to either the intervention or the control group. A secure computerized system will generate an unpredictable and concealed allocation sequence. A blinded researcher will manage this sequence in opaque envelopes, which will be opened after the participant’s enrollment and baseline measurements are complete.

To ensure group balance and methodological rigor within each stratum, we will use permuted blocks of sizes two and four (25). The block size and allocation sequence details will remain confidential and inaccessible to the team members involved in recruitment, treatment, and assessment until the conclusion of the study.

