#### Intervention group

2.5.1

Participants in the intervention group will use a digital speech therapy application designed explicitly for post-stroke dysarthria. Participants will use the application independently, without requiring continuous assistance from caregivers or medical professionals. In addition, occasional guidance or support from family members will be permitted. As part of our regular monitoring process, researchers will follow up on the extent of family assistance to ensure it remains appropriate and consistent for the therapy protocol. However, the primary aim is for participants to manage the therapy autonomously. This approach promotes independence and self-reliance during treatment. Participants will engage in speech therapy for 60 min each day, 5 days a week, for 4 weeks. The flexibility of the application should enable participants to complete their therapy in either a single session or multiple sessions throughout the day. Before therapy begins, researchers will introduce the application to participants and guide them through its usage. Additionally, we will provide a manual booklet to ensure that participants can use the application confidently and independently.

As the majority of stroke patients are older adults, the application is designed to be user-friendly (27). It features elder-friendly functionalities and provides progress updates through both text and voice descriptions to ensure accessibility. Design elements such as button size and spacing are tailored to accommodate the potential fine motor and vision challenges faced by older users (28).

Given the variability in speech impairment patterns due to different stroke lesions in post-stroke dysarthria (29), this application provides a personalized approach to speech therapy. When participants log into the application, it prompts them to perform four speech assessment tasks to evaluate their current speech conditions. The application uses a smartphone microphone to measure the ambient noise levels before each task to ensure optimal recording conditions. The assessment proceeds only if the noise level is <50 dB. Four assessment tasks were adapted from traditional dysarthria assessments. Each task comes with detailed instructions and sample demonstrations to help participants perform assessments efficiently.

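### As worded, the exploratory setting analysis compares app users in hospital with app users at home, so recovery and discharge timing can pass for a setting effect

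*Protocol article*

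**What the plan says.** Section 2.7 (Analysis) of the protocol article makes non-inferiority of app to workbook, on change in speech intelligibility, the primary objective. Subgroup analyses come in addition to it. The one on setting reads: "Subgroup analyses include comparing its use during hospitalization with post-discharge home use". The possessive points to the application, and no workbook comparator is named in that sentence. The stated purpose follows: "These analyses aim to provide a deeper understanding of how the setting influences the effectiveness of the therapy".

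Stroke phase is handled separately: "Furthermore, additional subgroup analyses will focus on the effects of the interventions across different stroke phases". The repeated-measures ANOVA is specified "with fixed effects for time, group, and their interactions", with no term for setting or phase.

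Other sections bear on this:

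- Section 2.3 (Randomization): "Participants will be randomly allocated in a 1:1 ratio to either the intervention group or control group". The only stratification factor is stroke phase, given as "acute to subacute phase (within 1 month of onset) and chronic phase (from 1 month to 6 months of onset".
- Section 2.5.1 (Intervention group): "Participants will engage in speech therapy for 60 min each day, 5 days a week, for 4 weeks".
- Section 2.6 (Outcome measurements): "Participants will engage in the post-evaluation phase 4 weeks after the baseline assessment". Table 2 places the speech outcomes at baseline and 4 weeks only; the close-out column holds usability alone.
- Table 3 lists days from stroke to enrolment. It lists neither treatment setting nor discharge date, though a condensed article may simply not show them.

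**The concern.** The randomisation protects app against workbook. It does not protect app users in hospital against app users at home. Three features make the second comparison fragile.

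1. Setting is neither randomised nor a stratum. The home category is defined by discharge, which for a participant enrolled as an inpatient can fall after randomisation and can depend on how well that participant is recovering.
2. There is one change score per participant. If the 4-week course is split between two places, that score belongs to neither.
3. Enrolment runs from the first month to 6 months after onset. If hospital users tend to be earlier after stroke, setting partly stands in for phase and for spontaneous recovery.

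At stake is a published statement about where the app works, which readers would take as an effect of setting on the therapy. The non-inferiority conclusion does not depend on it.

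**Working it through.** **Inputs from section 2.7.** SD 24.9; margin 19 points; one-sided alpha 0.025; power 80%; true difference 0; 28 evaluable per arm required. No sample size or precision is stated for the setting comparison.

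**The plan's own figure.** n = 2(1.960 + 0.842)² × 24.9² / 19² = 26.96 per arm, or 27 by the normal approximation. The t-based calculation gives 28 (power 80.1%). The stated 28 is reproduced, so 24.9 is used below as the SD of change.

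**Assumed inputs.** Discharge timing, the mix of settings, and recovery by phase are not in the documents. Everything below assumes no true setting effect.

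**(a) Discharge timing, app users only.** Let improvement have correlation ρ with earlier discharge, and let the earlier-discharged half count as home users. The spurious home-minus-hospital difference is 2ρ × SD × √(2/π) = 39.7ρ.

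| ρ | Formula | Simulation |
|---|---|---|
| 0 | 0 | 0.0 |
| 0.1 | 4.0 | 3.9 |
| 0.3 | 11.9 | 12.0 |
| 0.5 | 19.9 | 19.8 |

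The direction favours home.

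**(b) Stroke phase, app users only.** If early participants improve g points more than later ones, the spurious hospital-minus-home difference is g × (early share in hospital − early share at home).

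| Early share, hospital / home | g = 5 | g = 10 | g = 15 |
|---|---|---|---|
| 90% / 30% | 3 | 6 | 9 |
| 80% / 40% | 2 | 4 | 6 |
| 70% / 50% | 1 | 2 | 3 |
| 50% / 50% | 0 | 0 | 0 |

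The direction favours hospital. The first two rows span 2 to 9 points.

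**(c) App minus workbook within setting, same simulations as (a).** The arm-by-setting interaction is 0.2 points or less in absolute value at every ρ, because both arms share recovery and discharge selection. If the app has a true effect of 5 points and thereby speeds discharge, the effect seen within each setting falls to 4.7–4.8 at ρ = 0.3 and 4.1–4.2 at ρ = 0.5. That residual bias arises because setting is then decided after randomisation; fixing setting at randomisation removes it.

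**(d) Precision.** Within the app arm, SE = 24.9 × √(1/a + 1/b), where a and b are the numbers in each setting. With equal arms the interaction SE is √2 times that. The 95% CI half-width is 1.96 × SE.

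| Split per arm (assumed) | App users only | Arm-by-setting interaction |
|---|---|---|
| 14 / 14 (28 evaluable) | 18.4 | 26.1 |
| 8.4 / 19.6 (30% / 70% of 28) | 20.1 | 28.5 |
| 19 / 19 (all 38 recruited) | 15.8 | 22.4 |

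At 14 per cell, the interaction detectable with 80% power is 2.80 × 24.9 × √(2/14) × √2 ≈ 37 points.

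**The case against.** The case against has four parts.

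- **Status.** The comparison is a subgroup analysis added to the primary analysis. Setting is not among the aims in the Introduction, and no confirmatory conclusion rests on it. This stands.
- **Inference.** No section says that participants go home during the 4 weeks, how many do, or that setting follows stroke phase. One of the three sites is a rehabilitation centre, so inpatients beyond the first month are not ruled out. This also stands: both mechanisms are plausible, not documented.
- **Reading.** The surrounding text speaks of exploring influences on the primary efficacy results, which are app against workbook, and of the app's efficacy in various settings. On that reading shared recovery largely cancels, as (c) shows. This stands in part. The sentence that defines the comparison still sets one use of the app against another, and the next sentence draws a conclusion about setting from it. Even on the favourable reading, any difference in effect by setting stays entangled with phase.
- **Detail.** How setting is classified and modelled may sit in a full protocol or analysis plan that is not shown. True, so the absence of that detail is not the point made here. The point is the contrast that the article does state.

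A reader might infer that the hospital-versus-home question cannot be answered at all, that recovery will show up as a setting effect, or that almost no inpatient could be assigned to one setting. The documents do not support these. They give no discharge timing, the two biases pull in opposite directions, and an app-versus-workbook reading largely avoids the bias.

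**Conclusion.** The point holds for the contrast as written. A comparison of app users by where they used the app is non-randomised, may be defined by an event after randomisation, and rests on one post-baseline score. It can show a setting difference where there is none.

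Under the stated assumptions the spurious difference is about 4 to 20 points towards home from discharge timing (ρ from 0.1 to 0.5) and about 2 to 9 points towards hospital from phase imbalance. Either shrinks to zero if its premise fails, so the net size and sign are unknown. For scale, the upper end is about the size of the 19-point margin. This is a fault of wording and method in an exploratory analysis.

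**What to change.** In section 2.7 and the analysis plan:

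1. Define setting once, as inpatient or at home on the day of randomisation, and record it.
2. Estimate the app-minus-workbook difference in intelligibility change in each setting from one model with an arm-by-setting term and stroke phase, ideally also an arm-by-phase term. Report estimates with 95% confidence intervals.
3. Label the result exploratory, and drop or qualify the statement that it shows how setting influences effectiveness.
4. Present any comparison of app users by where they used the app as descriptive only. Recording the discharge date would let the split of sessions between hospital and home be described.

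The cost is wording and one or two data fields. There are two downsides. Setting at the start does not describe where every session took place. The interaction will also be imprecise, and an arm-by-phase term can widen it further where setting and phase are correlated. Setting remains unrandomised, so a difference in effect between settings would still be an association.
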